### 2.2. Measures and Experimental Procedure

#### 2.2.1. Demographics

Age, gender, training duration, medical history, the use of medication, (e.g., mental health issues), health habits (e.g., activity prior to blood draw, alcohol consumption, smoking), rugby playing history, position, and history of concussion will all be recorded at the outset. Personalized anthropometric measures, as well as stature and total body mass, will be recorded for each player using digitized coordinate data from whole-body static pictures. Body segment inertia properties, such as segment masses, moment of inertia, and total body mass center position, will be provided by these measures; the methods described in Gittoes et al., 2009, and Yeadon, 1990 [70,71], will be employed.

The measures and experimental procedures for (2) blood and (3) biomechanical and cognitive-motor tasks and (4) notational analysis are presented below in Section 2.2.2 and Section 2.2.3. The analysis of the data will be combined to address the specific multivariate nature of the research questions.

#### 2.2.2. Blood Methodology

Prior to the competition (the day before), 10 mL of blood will be collected from each player into two separate 5 mL serum separation vacutainer tubes (SSTs) (Becton Dickinson, Rutherford, NJ, USA). These samples will be collected at the same time of day to avoid diurnal effects. Consistency in timing, data collection, and standardization of experimental testing will also provide experimental rigidity and will be established using results from a pilot study prior to data collection.

On competition day, a 10 mL blood sample will be collected into two separate 5 mL SSTs prior to the first rugby game and then again immediately after each subsequent match. Following the final rugby match, blood will be immediately collected, in addition to further sampling at 24 h, 48 h, and 72 h later, also using two separate 5 mL SSTs. All blood samples will be taken using the venipuncture method. Blood will be collected and left to coagulate at room temperature for one hour. After incubation, the blood will be centrifuged at 1250× *g* for 10 min at 4 °C. On completion of centrifugation, the serum supernatant will be collected and kept at −80 °C in two tubes (Eppendorf^®^). Two separate Eppendorf tubes are a requirement, because the serum from both 5 mL SSTs will be kept at Cardiff Metropolitan University for analysis. One tube will facilitate the analysis of serum creatine kinase (CK), cardiac troponin T, and cortisol, while the serum from the other 5 mL SST will be used for the analysis of serum neuron-specific enolase (NSE), protein S100B (S100B), brain-derived neurotrophic factor (BDNF), glial fibrillary acidic protein (GFAP), and ubiquitin carboxyl-terminal esterase L1 (UCHL1). Keeping two separate vials will prevent freeze-thaw cycles and therefore maintain the integrity of the serum samples.

Serum NSE, cardiac troponin T, S100-B, and cortisol will all be measured by an electrochemiluminescence immunoassay using a Modular Analytics E analyzer, supplied by Roche Diagnostics; serum CK will be measured using a Specord 200 spectrophotometer with a Roche/Hitachi 917/MODULAR P analyzer; and BDNF, GFAP, and UCHL1 will be analyzed using an enzyme-linked immunosorbent assay (ELISA).

#### 2.2.3. Biomechanical and Cognitive-Motor Tasks

The methods below outline the procedures for the assessment of biomechanical and cognitive-motor task functions to examine the influence of concussion events during the rugby 7 s tournament. Prior to the rugby tournament, players will complete baseline tests for biomechanical and cognitive-motor tasks. Tests will be performed in a single battery, where players move between stations in a pseudo-random order.

Two categories of tests are explained: (1) whole-body movement and coordination testing and (2) cognitive-motor tasks. The NIRSIT (OBELAB Inc., Seoul, Republic of Korea) Brain Imaging System will be utilized simultaneously with the body movement assessment and cognitive tasks in monitoring, in real time, the brain condition. The NIRSIT is a wireless portable Functional Near-Infrared Spectroscopy (fNIRS) system, which (a) utilizes light to detect hemodynamic changes in the cerebral blood flow and (b) visualizes brain activation regions in the prefrontal area of the brain.

### 2.3. Experimental Procedure

#### 2.3.1. Whole-Body Movement and Coordination Testing

Four whole-body tasks will be completed within the motion capture area: an ecologically valid movement task (i. throwing task), (ii. tackle task), balance (iii. mBESS stance), dynamic balance (iv. tandem gait), and coordination (v. finger-to-nose task).

Throwing task: During the validated movement task, participants will undertake expected and unexpected passing practices in which they will run and pass at top speed to a target (Figure 2). During the anticipated pass, the player will start at a standstill and then will run forward 5 m at full pace to a performing zone, where they will throw a rugby-style pass to the left and right to a target 6 m away; this will be performed 3 times (3-left; 3-right). In the unanticipated task, a light (SMARTSPEED pro, Fusion sport, Australia) in front of the participant will indicate the direction of the pass in a pseudo-random order when they reach 0.5 m from the target line. A successful pass will be one that hits the target, as shown in Figure 2 and as evaluated by a National Performance Director. Data collection: during the whole-body movement and coordination tasks, participants will be labeled using a modified full-body 6-DOF kinematic model [72,73]; using double-sided tape, 38 retroreflective markers (14 mm in diameter) will be applied to the skin (Figure 3). Three-dimensional kinematic (14 cameras, Vicon Vantage Oxford Metrics, Oxford, UK, 250 Hz) and kinetic data will be obtained (force plates: four 600 mm × 900 mm Kistler 9287BA, Winterhur, Switzerland). All cameras will be calibrated to residual errors of <0.3 mm using a 240 mm calibration wand. Prior to further analysis, the external force signals will be amplified internally and aggregated with kinematic data using Vicon Nexus (v2.2.3) and filtered using a low-pass method (4th-order Butterworth, 60 Hz cut-off). Body segment inertia parameters will be based on work by De Leva (1996), as successfully used across a number of dynamic sporting movements [72,73,74].

Tackle task: A tackling drill, where a player performs a maximal tackle on a pad in full-vision and “late vision” conditions with right-left/high-low decision options, will be captured with high-speed video and used to estimate whole-body reaction time, decision making, and aspects of the tackle technique. The late-vision condition provides a constraint on the performer that is more ecologically valid and increases face validity.

mBESS: During the mBESS test, players will be told to stand on their non-dominant foot with their dominant leg kept in 30° hip flexion, 45° knee flexion, and a tandem stance for 30 s with their eyes closed and hands placed on the iliac crest. Players will wear shoes. The non-dominant leg will be determined for all subjects as the non-preferential leg when kicking a ball. Players will be instructed to stand on a force plate located within the capture area.

On completing the mBESS, participants will perform the finger-nose task in the tandem stance position (differs from SCAT 5) with a modified set of instructions from the SCAT5:

“I’m going to put your coordination to the test right now. Please stand on the force plate open your eyes and extend your arm in front of you (shoulder flexed to 90 degrees, elbow and fingers extended). When I provide the start signal, I want you to perform five successive finger-to-nose repetitions using your index finger contacting the tip of your nose, then swiftly and accurately returning to the starting position”.

Tandem gait: Players will be told to stand behind a starting line with their feet together and their shoes on. Players will walk heel-to-toe, with one foot’s toes contacting the heel of the next at each step, for 3 m (eyes open), and then turn 180° and return (total 6 m). A 38 mm wide (sports tape) 3 m line will outline the route on the floor. Participants will be corrected and asked to continue if they step off the line, have a space between their heel and toe, or touch or grab the examiner or an object.

Finger-to-nose: A finger-to-nose task will be performed within the data-capturing area in accordance with a modified SCAT 5 procedure, with the subject standing with both feet on the force plate. “I’m going to put your coordination to the test right now. Stand on both feet, eyes open, and your dominant arm extended in front of you. Perform five sequential finger-to-nose repetitions, touching the tip of the nose with your index finger on the start signal, then returning to the starting position. Execute the actions as quickly and properly as possible”. Cognitive-motor tasks are covered in Section 2.3.2.

Prior to the cognitive-motor exam, participants will take the Mini-Mental State Examination (MMSE), which consists of 30 questions that assess participants’ sense of orientation, attention, immediate and delayed recollection, language, and construction [75,76].

In order to examine cognitive function, a series of tasks will be performed (i. Pegboard; ii. Tapping Task; iii. Stroop word test; iv. reaction time task; v. working memory).

Purdue Pegboard: The Purdue Pegboard is used to explore bimanual finger and hand dexterity [66,67]. The Purdue Pegboard consists of two parallel rows of 25 holes, with pegs first inserted into two laterally positioned cups, followed by collars and washers first pushed into two central cups. Four subtests are performed. The first subtest entails placing as many pins as possible in the holes (from top to bottom) within a 30 s time constraint, first with the favored hand, then with the non-preferred hand, and finally with both hands. In the fourth subtest, the individual alternates between using both hands to construct “assemblies” of a peg, a washer, a collar, and another washer in 1 min.

Tapping Task: The finger-tapping test (FTT) is a lateralized coordination and motor speed test. To conduct the test, the palm will be taped to a flat board with fingers splayed. The index finger will then “tap” on a computer keyboard button. Participants will be instructed to tap each finger on the button as quickly as possible throughout a 10 s period. There will be three trials with each finger.

To increase the number on the counting device with each tap, the number of taps will be averaged over trials [77].

Stroop word test: The Stroop color test will be carried out on a computer with the help of the online demo test [78]. Participants will be seated comfortably at the computer workstation and will be instructed on how to conduct the test. The test will be a demonstration and take 2 min to complete. Participants will be required to say the words aloud, since verbal and cognitive performance has been reportedly related to mild concussion symptoms. Stroop will be run using both vocal and keyboard responses. The four colors red, blue, green, and yellow will be utilized to convey 40 words for 2 s each. To allow scoring after the test, a screen + camera capture of the Stroop word and the participant response will be used for the spoken response. The view of the video will include the participant and the Stroop word on the screen. In the keyboard response task, participants will respond to the four colors using the r, b, g, and y keys on the keyboard. We will then explore whether there is a correlation between keyboard and verbal scores and if one of these modes of answering is more affected by a blow to the head.

Reaction time task: To quantify reaction time, a computerized reaction time test will be performed. The test will be repeated 5 times with each hand; more information on the reaction time challenge may be found here [79].

Working memory: In the Digit Span Backward test, participants are shown a string of digits that must be repeated backward. According to the SCAT 5, the working memory score is determined from the temporal reactions to rising number strings [53]. The raw data will be used to calculate working memory.

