#### 2.4.2. Cognitive-Motor Tasks

The cognitive-motor tasks will be examined using the standard clinical procedure. Specifically, Stroop word test: Scores will be reported as the average response time in incompatible trials minus compatible trials. Reaction time task: The task will be scored digitally in milliseconds. Purdue Pegboard: The number of pins inserted in the time period for each hand determines the score for the pin (peg) insertion subtests. The total number of pairs of pins inserted determines the score for the bimanual condition. The assembly score is the number of components assembled (for more information on how to set up/run a test, check the extended usage instructions in the Scoring Application or on our website). Finally, Tapping Task: Timing, consistency, and frequency will be quantified.

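### The Stroop text gives different response rules for the spoken and keyboard modes, so as written the exploratory mode comparison confounds response mode with task rule

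*Protocol article*

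**What the plan says.** The Introduction of the protocol article names the Stroop as its test of executive function. The procedure is in Section 2.3.1, in the Stroop paragraph:

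- Spoken mode: "Participants will be required to say the words aloud, since verbal and cognitive performance has been reportedly related to mild concussion symptoms".
- Both modes are used: "Stroop will be run using both vocal and keyboard responses".
- Stimuli: "The four colors red, blue, green, and yellow will be utilized to convey 40 words for 2 s each".
- Spoken answers are scored afterwards from video: "To allow scoring after the test, a screen + camera capture of the Stroop word and the participant response will be used for the spoken response".
- Keyboard mode: "In the keyboard response task, participants will respond to the four colors using the r, b, g, and y keys on the keyboard".
- Use of the two modes: their scores are to be correlated, and the authors will explore "if one of these modes of answering is more affected by a blow to the head".

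Section 2.4.2 gives a single scoring rule, with no distinction by mode: "Scores will be reported as the average response time in incompatible trials minus compatible trials". It states no accuracy or error score. Nowhere does the article say that the spoken answer is the color shown rather than the word written.

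**The concern.** A Stroop difference score reflects executive interference when the player must give the display color and hold back the written word. The spoken instruction asks for the word and the keyboard instruction asks for the color. A tester who follows the text literally would run two different tasks under one name and score them with one formula.

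Two things are at stake. First, the spoken score may not measure what the Introduction wants from it. Second, a gap between the two modes, or a weak correlation between them, could come from the task rule instead of the way of answering. Neither can be repaired after data collection: if players have read words aloud, the video holds no color-naming responses to score.

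A smaller matter is that the time difference alone does not show whether a player kept speed by making more errors.

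**Working it through.** No stated figure is available to reproduce. The check sets the instructions beside the score and asks what each reading allows.

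**Step 1. Possible readings.** The spoken rule can be to say the written word (literal) or to say the display color (if the wording is loose). The keyboard rule can be to press for the display color (natural reading) or for the named color, since the sentence does not specify. That gives 2 × 2 = 4 combinations:

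| Spoken rule | Keyboard rule | Same task in both modes? | Difference score reflects color-naming interference in both modes? |
|---|---|---|---|
| display color | display color | yes | yes |
| written word | written word | yes | little in either |
| written word | display color (text as written) | no | keyboard only |
| display color | written word | no | spoken only |

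Only one of the four serves both purposes, and it is not the one that the words describe. The last column rests on a general premise about the task, not on a figure in the document: reading a word is the habitual response, so a conflicting display color disturbs it little. The third column does not need that premise.

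**Step 2. What the mode comparison estimates.** Let S(mode, rule) be the Stroop score, or its change from baseline. On the literal text the planned contrast is

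S(keyboard, color) − S(spoken, word) = [S(keyboard, color) − S(spoken, color)] + [S(spoken, color) − S(spoken, word)].

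The first bracket is the effect of mode and the second is the effect of task rule. S(spoken, color) is not collected, so the two brackets cannot be separated.

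**Step 3. How many sessions the instruction governs.** Section 2.1 and Table 1 place the battery at baseline (1), after each of three games (3), and at 24, 48 and 72 h (3): 1 + 3 + 3 = 7 sessions per player. With 40 players this is up to 40 × 7 = 280 sessions.

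**Step 4. List structure.** Forty words at 2 s each take 40 × 2 = 80 s, or 2 × 80 = 160 s for two modes. The paragraph gives a duration of 2 min (120 s). This does not settle whether each mode has its own full list. It is a reason to state the list structure, and the conclusion does not depend on it.

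**Step 5. What the difference leaves out (assumed figures).** Suppose 20 of the 40 words are incompatible and a player's errors on them rise from 1/20 = 5% to 6/20 = 30% while mean times stay the same. The stated score does not change. Similarly, times of 700 and 850 ms that become 800 and 950 ms give 850 − 700 = 150 ms and 950 − 800 = 150 ms, a change of 0. These numbers show how the formula behaves and are not estimates for this trial.

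**The case against.** The strongest reply is that the spoken instruction is loosely worded. The paragraph also calls the task a color test and describes one test with two ways of answering. The instruction itself goes on to explain why a verbal response is wanted. Scoring by compatible and incompatible trials presupposes a conflict task. The test is taken from a cited online demonstration, which may carry the operative rule. All of this is fair. It means that the document supports an inconsistent instruction, not proof that the wrong task will be run. It does not remove the problem, because the two rules on the page differ and nothing on the page says which governs.

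A reader might go further and infer that the spoken score will be about zero at every session, or that the mode comparison is invalid outright. The article gives no figure for the first, and the second holds only on the literal reading.

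A reader might also infer that the trial would miss general slowing after a match. It would not: Section 2.4.2 scores a separate reaction time task in milliseconds, and tapping, Pegboard and tackle measures also bear on speed. Removing overall speed is what a difference score is meant to do, and it is a recognised interference measure.

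On errors, the article does not say that they are discarded. The video would allow them to be scored, and a condensed article may leave this to a fuller document. That part is therefore a suggestion and not a fault.

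Finally, the mode comparison is exploratory and absent from the stated aims and hypotheses, and the Stroop is one of five listed cognitive tasks. That limits the stakes.

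**Conclusion.** The concern holds as an inconsistency between two stated response rules that share one score. If the text is followed literally, the spoken difference score carries little of the intended executive interference, and the keyboard-versus-verbal comparison confounds mode with task rule. If the spoken wording is loose and the keyboard response is to the display color, the design is sound and only the sentence needs correcting. The same change settles either case.

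The size of any distortion cannot be computed from the document. The reach is one outcome and one exploratory comparison, at up to seven sessions per player. It is worth correcting before testing starts, because a wrong instruction cannot be undone by re-scoring. The statement about confounding follows from the text alone. The statement about interference also needs the premise that word reading is little disturbed by display color.

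**What to change.** In Section 2.3.1, state one response rule for both modes: the player gives the display color, not the written word, aloud in one mode and by key press in the other. State that both modes use the same 40-item list structure, including the split between compatible and incompatible items. This costs one or two sentences.

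As a secondary addition in Section 2.4.2, report for each mode the mean correct-trial time on compatible trials, the same on incompatible trials, and the error rate, beside the difference score. State that longer times and higher error rates mean worse performance. The key presses and video already planned supply the data. The cost is some extra scoring and more Stroop variables to report.

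### The spoken Stroop is to be scored from video that shows the player, which can reveal group or session to the scorer and affect only one side of the spoken-versus-keyboard comparison

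*Protocol article*

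**What the plan says.** All of this is in the protocol article.

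- **Spoken Stroop (Section 2.3.1).** Answers are scored afterwards from a combined screen and camera recording. What the camera shows is specified: "The view of the video will include the participant and the Stroop word on the screen". The scorer is not identified.
- **Keyboard Stroop (Section 2.3.1).** "In the keyboard response task, participants will respond to the four colors using the r, b, g, and y keys on the keyboard". How these answers are timed and scored is not stated.
- **Comparison of modes (Section 2.3.1).** The authors will look at the correlation between the two sets of scores and "if one of these modes of answering is more affected by a blow to the head". This is introduced as exploration.
- **Stroop score (Section 2.4.2).** "Scores will be reported as the average response time in incompatible trials minus compatible trials". No separate score is given for the spoken mode.
- **Pass (Section 2.3.1).** "A successful pass will be one that hits the target, as shown in Figure 2 and as evaluated by a National Performance Director".
- **Tackle (Section 2.3.1).** High-speed video is "used to estimate whole-body reaction time, decision making, and aspects of the tackle technique". Neither a scorer nor a method is named.
- **Setting (Section 2.1).** Sport-group players are tested at a pitch-side laboratory directly after each of the three games, and they shower only once testing is over. Controls are squad members who do not play and are described as free of injury and fatigue. Both groups are tested at baseline and at the post-match sessions.
- **Expectation (Introduction, Discussion).** Cognitive-motor performance is predicted to fall as games accumulate. The Discussion names the Stroop test among those expected to worsen.

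**The concern.** Players cannot be blinded to whether they have played. When a person derives an outcome from a recording, it therefore matters what the recording tells that person. Here the plan chooses a view that includes the player. Someone filmed straight off the pitch is likely to look different from a rested control, or from the same player the day before. A scorer who recognises that state and expects decline may, without intending to, place response onsets or resolve unclear answers in the expected direction. Randomisation does not remove this, because the cue arises after allocation.

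The comparison of spoken with keyboard answers is the most exposed use of these data. Only the spoken side is stated to be scored from video of the player. A scorer effect tied to session or group would enter that side alone and could not be told apart from a true difference between modes. The two modes may also be timed by different methods, which adds measurement difference even with a wholly neutral scorer.

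**Working it through.** The plan gives no figure for scorer error, so there is none to reproduce on this point. The check has three parts.

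**1. Can the scorer see both cues that a surviving bias needs?** Write the observed score as S = mean RT(incompatible) − mean RT(compatible), from Section 2.4.2. Let the scorer add b_I to incompatible and b_C to compatible times. Then

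observed S = true S + (b_I − b_C).

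- If b_I = b_C, the scorer effect is zero, whatever its direction.
- If b_I − b_C is not zero but is the same at every session and in both groups, it cancels in the change from baseline and in the group contrast.
- What survives in a player's change is (b_I − b_C) post-match minus (b_I − b_C) at baseline. In the group contrast it is the sport-group value of that quantity minus the control value.

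So the shift must differ by trial type and also by session or group. The specified view can supply both cues: the displayed word shows trial type, and the player may show state. Taking the player out of view removes the main source of the second cue.

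**2. The comparison of modes.** The observed spoken-minus-keyboard difference in change equals the true mode difference, plus the surviving scorer term for spoken answers, minus any such term for keyboard answers. If key presses are logged by the computer (likely, but not stated), the last term is zero and nothing offsets the spoken term.

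**3. How large would a net shift have to be?** The size is an assumption, shown as a range. Inputs are 20 per group (Section 2.1), two-sided 0.05 (Section 2.5), zero true effect, and a net shift of b SD in the analysed score.

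- Between groups: noncentral t with 2 × 20 − 2 = 38 degrees of freedom and noncentrality b√(20/2). For b = 0.3 this is 0.3 × 3.162 = 0.949.
- Within the sport group, with b in SD of the change: noncentral t with 19 degrees of freedom and noncentrality b√20. For b = 0.3 this is 0.3 × 4.472 = 1.342.

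| Assumed net shift b | False-positive rate, between groups | False-positive rate, within sport group |
|---|---|---|
| 0 | 5.0% | 5.0% |
| 0.1 SD | 6.1% | 7.1% |
| 0.2 SD | 9.5% | 13.6% |
| 0.3 SD | 15.2% | 24.7% |
| 0.5 SD | 33.8% | 56.5% |

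These are rates for a single simple t-test. They are not a model of the planned mixed-model analysis.

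**Passes.** There are 3 left and 3 right anticipated passes, so one borderline call moves anticipated-pass success by 1/6 = 16.7 percentage points. The number of unanticipated passes is not stated; including them would make the step smaller.

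**The case against.** The strongest reply is that a condensed article need not set out masking logistics, so silence on coded files or masked scorers is no fault. That is right, and this point does not rest on silence. It rests on the camera view that the article does specify, and on the comparison that then uses scores from that view.

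Other replies also stand in part:

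- **A reader might infer that the scorers know group and session.** The article does not say so. It places the participant seated at a workstation and does not mention kit or marks. The setting in Section 2.1 makes state guessable, and no more can be claimed.
- **A reader might infer that scorer expectation creates the post-match decline.** The response-time difference in Section 2.4.2 removes uniform shifts, and small net shifts inflate error only slightly. Counting misjudged words would not describe this bias either, because the defined score is not an error rate.
- **A reader might put passes and tackles on the same footing.** A target hit is a largely objective criterion even when judged by a person, so only borderline calls are open. The Discussion also expects passing accuracy to hold up to a critical point, so the expectation there is not uniformly of decline. For tackles, the article does not say whether a person or software derives the measures. If a person rates decision making and technique, these are the most judgement-dependent of the three outcomes.
- **Masking is not the sole safeguard.** Objective criteria and digital timing also protect.
- **The comparison of modes is exploratory.** This limits the consequence but does not make the result interpretable.

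**Conclusion.** A limited point holds. The article fixes a recording for later scoring of the spoken Stroop that shows the player, in a setting where the player's appearance can reveal group or session and where decline is predicted. It then compares that mode with one not stated to be scored in this way. Scorer shifts that differ by trial type and by session or group could contribute to an apparent decline or to a spoken-keyboard difference.

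The size is unknown. At an assumed net shift of 0.1 SD the effect on the false-positive rate is slight. At 0.3 SD the rate is about three times nominal between groups (15.2/5 = 3.0) and about five times within the sport group (24.7/5 = 4.9). This assumes that a person times or judges the spoken answers and can read state from the video. That the two modes are timed differently further assumes that keyboard answers are logged by the computer. Blood assays and the reaction time task, which Section 2.4.2 says is scored digitally, are not affected.

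**What to change.** - Score the spoken Stroop from audio onset plus the screen view only, with the player cropped out or not framed.
- Give clips coded names, shuffle them across players, groups and sessions, and have them scored after collection ends by an existing team member masked to group and session.
- State that the spoken-versus-keyboard comparison uses these masked scores, and that timing methods differ between the modes if they do.
- If a person rates the tackle clips, apply the same coding and shuffling. The player remains recognisable, so masking there will be partial.
- Where a pass call is borderline, read the target hit from coded video of the target.

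The cost is file renaming, cropping and shuffling, and no same-day scores. The tests themselves do not change. The camera framing is best settled before recording starts; coding, cropping and shuffling can follow. A voice may still betray breathlessness, so audio-based masking reduces the cue but may not abolish it.
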